**Fig. 1 Fig1:**
[figure not shown]
CONSORT flow diagram

### Sample size {14}

To ensure sufficient power for the effects at all time points, we considered potential dropout and power analysis for the last follow-up time point after 6 months (T3) using G*power. Dropout for patients with a depressive disorder in IBIs over the course of 6 months was estimated to be 50% based on previous literature [53]. For smartphone-based interventions targeting depressive symptoms, meta-analyses found small (*g* = 0.28, [54]) to small-to-moderate (*g* = 0.383, [55]) effect sizes when comparing apps to control conditions. As the TAU group in our study must be considered an informed TAU group due to the screening process, the calculation of our sample size is conservatively based on a small effect size (*d* = 0.3). The sample size calculation is conservatively based on a small effect size (*d* = 0.3), as the TAU group must be considered an informed TAU group due to the screening process. To find this effect in a randomized controlled trial with a one-tailed *t*-test (alpha error level = 5%, power = 0.80) for independent samples, *n* = 139 participants per treatment group (total *n* = 278 participants) are needed to complete the t3 assessment. Considering the dropout rate, a total sample of *N* = 556 participants is needed at the time of randomization (1:1 randomization: *n* = 278 participants in IG; *n* = 278 participants in TAU).

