## Statistical methods

### Statistical methods for primary and secondary outcomes {20a}

It is possible that some participants may not utilize the app, despite being assigned to the intervention group, and yet still participate in the surveys (non-compliance). We will deal with non-compliance in the analyses in two different ways. For the primary analyses, we will include data from all randomized patients and evaluate both (1) the effect of assignment to the intervention and (2) the effect of the intervention itself. For the estimation of the causal effect of the assignment to intervention on the primary and secondary endpoints (intention-to-treat analysis), the mean values between the two study groups at T1, T2, and T3 will be compared using *t*-tests and MANOVAs within the framework of structural equation models (SEM). For estimating the causal effect of the intervention itself on the primary and secondary endpoints, we treat all participants who were assigned to the intervention group but did not use the app (and did not drop out before the measurement of the first endpoint) as members of the control group (as-treated analysis). As this invalidates randomization, we will control for selection bias by adding the variables measured at baseline as covariates in the model. We assess all endpoints also at baseline, as this helps to assure the ignorability assumption (e.g., Cook, Steiner, & Pohl, 2010). Assumptions on distribution and homoscedasticity are tested and, if violated, relaxed (by using respective estimators or multi-group modeling).

To investigate the utilization of care services, means on individual items of the FIMPsy will be compared between the two treatment groups via *t*-tests in SEM.

For the intervention group, usability and acceptance of the intervention are analyzed using descriptive statistics to describe satisfaction (CSQ-i, SUS) and utilization behavior. The different recruitment channels for the intervention are surveyed and descriptively analyzed.

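### The 80% power at t3 requires a one-tailed 5% t-test and a true effect of at least 0.3; the analysis section does not commit to that test, and the plan's own evidence does not make 0.3 conservative

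*Protocol article*

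**What the plan says.** Sample size {14} of the Protocol article sizes the trial at its last assessment (t3, 6 months) so that every time point is adequately powered.

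- **Evidence on the effect:** "meta-analyses found small (*g* = 0.28, [54]) to small-to-moderate (*g* = 0.383, [55]) effect sizes" for apps against control conditions.
- **Effect chosen:** "the calculation of our sample size is conservatively based on a small effect size", d = 0.3. The reason given is that screening turns the control arm into an informed TAU group. The next sentence repeats the statement.
- **Test:** "To find this effect in a randomized controlled trial with a one-tailed" t-test for independent samples ("alpha error level = 5%, power = 0.80").
- **Result:** 139 "participants per treatment group (total *n* = 278 participants) are needed to complete the t3 assessment".
- **Dropout:** "over the course of 6 months was estimated to be 50% based on previous literature", which takes 278 completers to 556 randomized, 278 per arm.

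Statistical methods {20a} compares group means at T1, T2 and T3, for primary and secondary endpoints, by t-tests and "MANOVAs within the framework of structural equation models (SEM"). It states no sidedness. Outcomes {12} singles out t1 as the time point that matters most for the EPDS. Section {20c} handles dropout by full information maximum likelihood (FIML), with the baseline variables as auxiliaries.

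**The concern.** Two things do not fit together.

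First, the sample size rests on a one-tailed test, but the analysis section does not adopt one. A t-test can be run either way. An omnibus MANOVA F test cannot be one-tailed at all. At least part of the planned analysis is therefore not the test that was powered. If sidedness is still open when data arrive, the choice could follow the result. A one-tailed 5% test also allows a false-positive rate of 5% in the direction of benefit, against 2.5% for a two-sided 5% test.

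Second, a conservative effect size should lie at or below the lowest credible estimate. The plan's 0.3 lies above its own lower estimate of 0.28. Its reason for caution, a better-informed control group, points to a smaller effect.

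At stake is a stated property of the design: a cautious basis that secures 80% power up to t3.

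**Working it through.** **Inputs**, all from {14}: d = 0.3; cited effects 0.28 and 0.383; alpha 5%; power 80%; 139 completers per arm; 50% dropout; 278 randomized per arm.

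**Formula.** For two independent means with n per arm, the noncentrality is d × √(n/2) on 2n − 2 degrees of freedom, and power comes from the noncentral t distribution.

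**Step 1: the plan's own figure.** With n = 139, √(139/2) = 8.337, so the noncentrality at d = 0.3 is 2.501. One-tailed 5% power on 276 degrees of freedom is 80.2%, and 139 is the smallest n that reaches 80%. Then 278 / (1 − 0.50) = 556. Both figures reproduce.

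**Step 2: change sidedness and effect.**

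| True d | Noncentrality | Power at 139 per arm, one-tailed | Power at 139 per arm, two-sided | n per arm for 80%, one-tailed | n per arm for 80%, two-sided |
|---|---|---|---|---|---|
| 0.28 | 2.334 | 75.3% | 64.3% | 159 | 202 |
| 0.30 | 2.501 | 80.2% | 70.3% | 139 | 176 |
| 0.383 | 3.193 | 93.8% | 88.9% | 85 | 108 |

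Holding 80% at t3 with 50% dropout would need 4 × 176 = 704 randomized (d = 0.30, two-sided), 4 × 159 = 636 (d = 0.28, one-tailed) or 4 × 202 = 808 (d = 0.28, two-sided). These show the scale of the gap. They are not a proposal to recruit more.

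**Step 3: MANOVA, illustration only.** Take the EPDS at T1 to T3, the same d at each time, 139 per arm and a common between-time correlation r. Hotelling's test has noncentrality (n/2) × 3d² / (1 + 2r) on 3 and 274 degrees of freedom. At d = 0.3:

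- r = 0.3: 69.5 × 0.27 / 1.6 = 11.73, power 82.5%
- r = 0.5: 69.5 × 0.27 / 2.0 = 9.38, power 72.4%
- r = 0.7: 69.5 × 0.27 / 2.4 = 7.82, power 63.6%

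The correlations are assumed, because the protocol gives none.

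**Step 4: t1.** Two-sided 80% at d = 0.3 needs 176 completers per arm. 176 / 278 = 63.3%, so up to 36.7% loss is tolerated. At d = 0.28 the need is 202; 202 / 278 = 72.7%, so up to 27.3% loss is tolerated. With no loss (278 per arm), two-sided power is 94% at d = 0.30 and 91% at d = 0.28.

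**Step 5: possible gain from baseline EPDS, illustration only.** If baseline acts as a covariate with correlation r to the outcome, the effective effect is d / √(1 − r²). At 139 per arm, two-sided:

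- r = 0.3: power 74% (d = 0.30) and 68% (d = 0.28)
- r = 0.5: power 82% (d = 0.30) and 77% (d = 0.28)

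These correlations are assumed too.

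**The case against.** The defence has real substance.

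- **The sample size is not miscalculated.** The one-tailed basis is disclosed, the figures reproduce, and a directional test is coherent with a superiority question. Preferring two-sided 5% is a convention. This stands: a reader might infer an arithmetic error, and there is none.
- **Lower power is not a fact about the trial.** A reader might infer that true t3 power is 64% to 75%. Those figures need a two-sided test, a true effect of 0.28, or both, and the protocol fixes neither. At its upper cited effect, power is 89% to 94%.
- **The MANOVA may not carry the EPDS claim.** Section {20a} names t-tests and MANOVAs together for all endpoints. The MANOVA figures depend on assumed correlations and exceed 80% at r = 0.3. They also apply t3 completer numbers to T1 and T2, where more data may exist. So they do not show that the MANOVA is underpowered. The absence of direction in that test stands regardless.
- **Efficiency is left out.** FIML with baseline EPDS among the auxiliaries could recover power. That is possible, but {14} claims no such gain, and its size depends on correlations that are not given and on how baseline enters the model.
- **0.3 is near the bottom of the cited range.** It lies below the midpoint, (0.28 + 0.383) / 2 = 0.33, and only 0.02 above the lower end. That gap still costs about 5 points of one-tailed power (80.2% to 75.3%), and the stated reason argues for going lower.

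A reader might also take the roughly 6% risk of worsening, cited under Adverse event reporting {22}, as proof that a two-sided test is required. It does not support this: it concerns deterioration during internet-based treatment and is cited for safety. It is not a difference in means between arms.

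**Conclusion.** The point holds as an internal mismatch and an unsupported description of the design. The 80% at t3 is correct only for a one-tailed 5% t-test with a true effect of 0.3 or more. Section {20a} does not commit to that test and adds one that cannot be directional. Section {14}'s own lower estimate and its own reasoning contradict the word *conservatively*. With 139 completers per arm and no baseline adjustment, moving to a two-sided test costs about 10 points (80.2% to 70.3%). Moving to d = 0.28 costs about 5 points one-tailed, and both together cost about 16 (to 64.3%). These figures assume exactly 50% loss by t3 and an analysis of completers only. At t1 the same N is adequate for a two-sided test at d = 0.3 if loss stays at or below 36.7%; the protocol gives no loss figure for t1.

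**What to change.** Keep N = 556 and change the text:

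1. State the same sidedness in {14} and {20a}, preferably two-sided 5%, before any outcome data are seen.
2. Tie the main EPDS claim to the t1 comparison that {12} already puts first. State that 176 completers of 278 per arm give two-sided 80% at d = 0.3, which allows up to 36.7% loss at t1.
3. Report t3 power at 50% loss as about 70% (two-sided, d = 0.3) and 64% (two-sided, d = 0.28), before any gain from baseline EPDS.
4. Delete *conservatively* in both sentences of {14} where it occurs, and qualify or remove the claim of adequate power at every time point.

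The cost is wording and a less favourable stated power at t3. No further participants are needed.

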### Recruitment {15}

To ensure adequate participant enrollment, we will use several recruitment channels. (1) Social media channels will be used to provide information about the study through regular posts and stories, and ads will be placed on social media linking to the registration website. (2) Maternity clinics, midwives, gynecologists, and pediatricians will be recruited throughout Germany during the first year of the project to inform women about the intervention in routine care and to invite them to participate in the study. Pediatricians and midwives should be well acquainted with the offer and be able to provide information about it. For this, they receive an expense allowance from the project. The clinics should make women aware of the offer and inform them about it before birth or during the so-called U2 examination that routinely takes place at 3–10 days after birth in Germany. (3) Participating health insurance providers will inform women after birth as part of the routine information package that all women receive after the childbirth to draw attention to special services and offers provided by the respective health insurance provider.

## Assignment of interventions: allocation

### Sequence generation {16a}

A randomization list will be provided to the DIRECT software developers by a third party and entered into the system. There is no possibility for the stakeholders of the study to access/see this list. Participants meeting the inclusion criteria are randomly allocated to one of the groups by the trial staff via clicking a button in the admin panel. The randomization list is computer-generated using permuted block randomization using the “block rand” package in R. The sequence is generated by an external researcher and directly sent to the software developers who are adding the randomization list to the study.

### Concealment mechanism {16b}

After participants complete their baseline assessment, the coordinator is able to randomize the participant into intervention or TAU groups via a button on the admin panel without any knowledge of the order in the randomization list. The randomization list cannot be accessed or changed by the study team. After participants complete the baseline assessment, they are randomized by pressing a button in the study admin panel (i.e., a web application that is used by the study team to manage the study). This button assigns the participant to the next free seat on the randomization list. Since the randomization list is not accessible to the study team, it is not known what group a participant will be assigned to, prior to pressing the button.

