## Assignment of interventions: blinding

### Who will be blinded {17a}

Due to the nature of psychotherapeutic intervention trials, neither participants nor therapists can be blinded to treatment allocation. Biostatisticians remain blinded to allocation.

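### A hidden randomisation list does not by itself make the next assignment unknown: with permuted blocks, open allocation and a hand-pressed button, the next arm can be guessed better than chance

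*Protocol article*

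**What the plan says.** Under Sequence generation {16a}, an external researcher produces the list and sends it straight to the software developers. On the method: "The randomization list is computer-generated using permuted block randomization using the “block rand” package in R". One list is described, and no stratification is mentioned. Participants are "randomly allocated to one of the groups by the trial staff via clicking a button in the admin panel".

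Concealment mechanism {16b} places this step after the baseline assessment, when "the coordinator is able to randomize the participant into intervention or TAU groups via a button on the admin panel". It adds: "This button assigns the participant to the next free seat on the randomization list". The panel that holds the button is described as the study team's tool for managing the trial. The section then draws its conclusion: "Since the randomization list is not accessible to the study team, it is not known what group a participant will be assigned to" before the button is pressed.

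Implementation {16c} repeats that study administrators randomise in the panel once baseline is complete. Under Who will be blinded {17a}, "neither participants nor therapists can be blinded to treatment allocation". Only the biostatisticians are said to be blinded.

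The article gives no order or time limit for pressing the button, and does not say whether those who press it are kept from seeing earlier assignments.

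**The concern.** Hiding the list is necessary for concealment, but with restricted randomisation it is not sufficient. Within a permuted block the arm that has fallen behind is more likely to come next, so a person who knows past assignments learns something about the next seat without seeing the list.

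That knowledge matters only if it can be acted on. Here allocation is a separate manual step after baseline, EPDS included, and the woman for whom the button is pressed takes the next seat. If two or more women are waiting, the order of pressing decides who takes which seat. Bad faith is not needed: only the intervention arm requires a therapist, so therapist availability could be an ordinary reason to time a press. If the order came to depend on a woman's characteristics and on the arm expected next, the groups would differ at baseline for reasons other than chance, and the intention-to-treat comparison would lose part of what randomisation is meant to secure.

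**Working it through.** **The plan's own figures.** The article gives no figure for predictability. The trial size used below does reproduce: for d = 0.3, one-sided alpha 0.05 and power 0.80 (Sample size {14}), the exact noncentral t gives power 0.7998 at 138 per arm and 0.8023 at 139, so 139 per arm and 278 completers; 278 / (1 − 0.5) = 556. This point does not change it.

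**Inputs.** From the article: 1:1 allocation, one permuted-block list, 556 seats, next free seat taken at each press. Assumed: block sizes 2 to 10 (none stated), and an observer who knows past assignments but never sees the list.

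**Correct-guess rate, fixed blocks.** The observer always names the arm that is behind and guesses at random when the arms are level. For block size 2m the expected number of correct guesses per block is m + 2^(2m−1) / C(2m, m) − 1/2. Divide by 2m for the rate. The share of seats known with certainty, for someone who also knows the fixed size, is 1/(m + 1).

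| Block size | Expected correct per block | Correct-guess rate | Certain, if size fixed and known |
|---|---|---|---|
| 2 | 1 + 2/2 − 0.5 = 1.500 | 75.0% | 50.0% (278 of 556) |
| 4 | 2 + 8/6 − 0.5 = 2.833 | 70.8% | 33.3% (about 185) |
| 6 | 3 + 32/20 − 0.5 = 4.100 | 68.3% | 25.0% (139) |
| 8 | 4 + 128/70 − 0.5 = 5.329 | 66.6% | 20.0% (about 111) |
| 10 | 5 + 512/252 − 0.5 = 6.532 | 65.3% | 16.7% (about 93) |

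**Mixed blocks, sizes equally likely.** The same strategy needs no knowledge of the sizes. Its rate is the sum of expected correct guesses over the sum of sizes:

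- {2,4,6}: 8.433 / 12 = 70.3%
- {4,6}: 6.933 / 10 = 69.3%
- {4,6,8}: 12.262 / 18 = 68.1%
- {2,4,6,8}: 13.762 / 20 = 68.8%

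Certainty nearly disappears. In simulation (200 lists of 556 seats, observer knowing the set of possible sizes) it was 5.5% for {4,6}, 2.3% for {4,6,8} and 2.1% for {2,4,6,8}. Unrestricted 1:1 randomisation gives 50% and 0%.

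**Could women be waiting together?** Trial status plans first enrolment on 15/08/2024 and completion around 30/04/2025, which is 258 days. 556 / 258 = 2.16 per day, or about 15 per week. Waiting together is possible at that rate. The article does not say how often the button is pressed.

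**Illustration of a baseline difference.** Suppose two women are always waiting. Whenever one arm is behind, the milder woman is placed if the intervention is due and the more severe one if TAU is due; the other stays in the queue. The baseline score is standard normal, with 556 seats.

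- Acted on at every such seat: 0.56 / 0.35 / 0.27 / 0.21 SD for blocks of 2 / 4 / 6 / 8
- Acted on at a quarter of such seats: 0.14 / 0.07 / 0.05 / 0.04 SD
- Mixed {2,4,6}: 0.35 and 0.07 SD respectively

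A repeat run agreed within 0.01 SD. Assignment in order of baseline completion gives 0 for this mechanism.

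**From baseline difference to outcome.** Let D be the baseline difference (intervention milder), r the baseline–outcome correlation, and the SDs equal. Follow-up means are shifted by r × D in favour of the intervention. Change scores are shifted by (1 − r) × D against it. With r = 0.5 (assumed) and D = 0.04 to 0.14, both shifts are 0.02 to 0.07 SD, in opposite directions. The article names both comparisons: change from baseline under Outcomes {12}, and group means at T1, T2 and T3 under Statistical methods {20a}.

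**The case against.** The safeguards are substantial. The sequence is made outside the team, which can neither view nor change it. Consent, screening and baseline are finished before allocation, and baseline data are self-reported in the app, so foreknowledge cannot steer enrolment or scores. This stands, and it leaves only the order or delay of pressing.

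The article nowhere says that coordinators follow past assignments or may pick among waiting women. This also stands. Knowledge of earlier assignments is likely, since the person pressing sees each result, the arms are paid differently and only biostatisticians are described as blinded. It is still an inference, and silence on queue order is not permission.

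A reader might infer that staff often know the next arm outright. The documents do not support that. The 17% to 50% certainty figures need a fixed block size that staff know; with varied sizes certainty is about 2% to 6%. An article may properly leave block sizes to the full protocol, so their absence is not the fault here.

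A reader might also set 0.04 to 0.14 SD against the d = 0.3 used for sizing and read it as a share of the effect. That would require a baseline–outcome correlation of 1 and would ignore the change-from-baseline comparison, under which the sign reverses. The baseline variables used as auxiliaries under {20c} are a device for missing data and do not in themselves adjust the intention-to-treat contrast.

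**Conclusion.** The concern holds in a limited form. The conclusion in {16b} does not follow from its premise: for every block size tried, fixed or mixed, a person aware of past allocations beats chance without seeing the list, at about 65% to 75% against 50%. This rests on assumed block sizes and on an observer who knows earlier assignments.

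The documents do not show that concealment will fail or that selection will occur. They describe a manual step that leaves open one route, the order or delay of pressing, and a sentence that treats that route as closed. The size of any bias is unknown. The 0.04 to 0.14 SD baseline differences are a scenario, not an estimate; they do not carry one-for-one into the outcome and could favour either arm. Severity is minor to moderate, and the case for acting is mainly that the remedy is cheap.

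**What to change.** In {16a} to {16c}:

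- Have DIRECT assign the next seat automatically, with a time stamp, in order of baseline completion, once eligibility and any required safety call are settled. If the button stays, enable it only for the earliest eligible completer.
- State that block sizes vary and are withheld from the study team. The sizes themselves need not be published. Simple randomisation is an option rather than a requirement: with 556 women the SD of an arm's size would be √(556 × 0.25) = 11.8 around 278.
- Reword the concealment sentence so that it rests on the hidden list together with the fixed order of assignment and the undisclosed block sizes, and not on list access alone.

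The cost is a small software rule and changed wording, with no extra participants. The rule has to be fitted around the existing telephone calls: screening signals lead to a call under Participant timeline {13}, and the EPDS with its self-harm item is repeated at baseline, so a woman whose call is pending must be held without blocking those behind her. Varying the block sizes may mean regenerating the list before first enrolment.
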